## Abstract

**Background:**

Comorbidities such as undernutrition and parasitic infections are widespread in India and other tuberculosis (TB)-endemic countries. This study examines how these conditions as well as food supplementation and parasite treatment might alter immune responses to *Mycobacterium tuberculosis* (Mtb) infection and risk of progression to TB disease.

**Methods:**

This is a 5-year prospective clinical trial at Jawaharlal Institute of Post Graduate Medical Education and Research in Puducherry, Tamil Nadu, India. We aim to enroll 760 household contacts (HHC) of adults with active TB in order to identify 120 who are followed prospectively for 2 years: Thirty QuantiFERON-TB Gold Plus (QFT-Plus) positive HHCs ≥ 18 years of age in four proposed groups: (1) undernourished (body mass index [BMI] < 18.5 kg/m^2^); (2) participants with a BMI ≥ 18.5 kg/m^2^ who have a parasitic infection (3) undernourished participants with a parasitic infection and (4) controls—participants with BMI ≥ 18.5 kg/m^2^ and without parasitic infection. We assess immune response at baseline and after food supplementation (for participants with BMI < 18.5 kg/m^2^) and parasite treatment (for participants with parasites). Detailed nutritional assessments, anthropometry, and parasite testing through polymerase chain reaction (PCR) and microscopy are performed. In addition, at serial time points, these samples will be further analyzed using flow cytometry and whole blood transcriptomics to elucidate the immune mechanisms involved in disease progression.

**Conclusions:**

This study will help determine whether undernutrition and parasite infection are associated with gene signatures that predict risk of TB and whether providing nutritional supplementation and/or treating parasitic infections improves immune response towards this infection. This study transcends individual level care and presents the opportunity to benefit the population at large by analyzing factors that affect disease progression potentially reducing the overall burden of people who progress to TB disease.

*Trial registration* ClinicalTrials.gov; NCT03598842; Registered on July 26, 2018; https://clinicaltrials.gov/ct2/show/NCT03598842

**Supplementary Information:**

The online version contains supplementary material available at 10.1186/s12879-021-06734-z.

## Background

Tuberculosis (TB) is one of the most common infectious causes of death worldwide resulting in 1.2 million deaths in 2019 [1]. One-quarter of the world is infected with *Mycobacterium tuberculosis* (Mtb) and 10% of these individuals develop TB over a lifetime [1]. India has a quarter of the global TB burden with 2.64 million cases and 436,000 deaths in 2019 [1]. The Indian government has committed to an 80% TB incidence reduction by 2025 [2]. However, even as the Indian government invests in improved testing, it has not made commensurate efforts in addressing the leading risk factor for the spread of TB in India: undernutrition. This is a critical shortcoming because more than 50% of TB cases in India are attributable to undernutrition [3], and in Puducherry, as many as 61.5% of TB cases in women and 57.4% in men are attributable to undernutrition [4].

Undernutrition is widely prevalent in India—the World Bank reported in 2018 that 14% of India’s total population was undernourished [5] with the National Family Health Survey reporting 22% and 19% of men and women, respectively, with low BMI in 2017 [6]. A recent systematic review found a log-linear relationship between BMI and TB incidence with a 14% decrease in TB incidence with every unit increase of BMI [7]. Furthermore, a longitudinal study in the United States found that having BMI < 18.5 kg/m^2^ is associated with an adjusted hazard ratio of 12.43 for developing TB disease compared to those with BMI ≥ 18.5 kg/m^2^ [8]. In addition, undernutrition is associated with increased risk of TB treatment failure and mortality [9], greater lung involvement in TB disease [10], and risk of drug-associated toxicities despite weight-based dosing [11].

Our understanding of how undernutrition affects the immune response to Mtb is limited. Animal models suggest undernutrition has an impact on innate and adaptive response [9] affecting macrophage mobility, chemotaxis, attachment, and phagocytosis [12]. Human studies of undernourished individuals showed that CD4^+^ and CD8^+^ T-cells needed for an effective T-helper (Th)-1 response may be sequestered in lymph nodes at the expense of the peripheral circulation [13] and that Th1 cytokine responses (needed to control Mtb infection) are decreased in such individuals [14, 15]. Detailed data on these mechanisms are lacking and hence it is not clear how exactly undernutrition impairs the immune responses. Research on the benefits of nutritional supplementation for TB prevention has heretofore primarily focused on vitamin D [16–19] with limited research on macronutrient or other micronutrient supplementation [20].

Undernutrition from inadequate caloric intake due to food insecurity can be exacerbated by parasitic infections that are common in India [21]. Intestinal parasites can decrease absorption of key macronutrients such as proteins and fats as well as micronutrients like zinc and iron [21]. Moreover, animal and human studies have shown that parasites can decrease food intake by inducing gastrointestinal symptoms such as nausea and diarrhea and increasing expression of cytokines like TNF-α and IL6 [7].

The Tuberculosis—Learning the Impact of Nutrition (TB LION) study thus aims to define the specific points at which undernutrition, parasitic infection and Mtb infection intersect, by identifying the mechanisms of the interaction and the response to intervention. These study findings will have relevance in India and other TB-endemic countries worldwide.

## Methods/design

### Aims, objectives, and outcomes

TB LION addresses four aims and outcomes: (1) Examine the effect of undernutrition and parasitic infections on innate and adaptive immune responses, Mtb killing and antigen-specific memory T cell responses in adult household contacts of patients with active TB; (2) Perform whole blood transcriptomics to gain insight into mechanisms of how malnutrition and parasitic infections modulate the immune response to Mtb infection and compare TB risk signatures in these groups; (3) Examine the effect of nutritional supplementation and (4) parasite treatment, on the above immune responses and RNAsequencing signatures.

### Study design and setting

TB LION is a prospective, exploratory clinical trial conducted at the Jawaharlal Institute of Postgraduate Medical Education and Research (JIPMER) in partnership with Boston Medical Center/Boston University and Rutgers New Jersey Medical School. JIPMER is located in Puducherry, India, a city of approximately 1.2 million [22]. TB LION enrolls participants across Puducherry and two districts of Tamil Nadu: Cuddalore (population ~ 2.6 million), and Villapuram (population ~ 3.5 million). Three field teams comprised of trained social works and nurses are responsible for study enrollment and participant follow up. Enrollment began in Puducherry in July 2019.

### Study population

Study staff identify new TB index cases (ICs) through the National Tuberculosis Elimination Programme (NTEP). Inclusion criteria are: (1) Age ≥ 18 years; (2) New sputum-smear positive (≥ 1+ acid fast bacilli [AFB]) pulmonary TB that is culture or GeneXpert positive; (3) No history of TB treatment; (4) Have at least one household contact (HHC) with whom they shared a house during the previous month; (5) Agree to have HHCs contacted. Exclusion criteria include: (1) Pregnant; (2) No GeneXpert or culture confirmation and unable to provide sputum sample; (3) No HHCs; (4) Known MDR or XDR TB; (5) BMI < 14 kg/m^2^ as to avoid refeeding complications; (6) Kwashiorkor, lower extremity edema or lower extremity neuropathy in those with BMI < 14.

Inclusion criteria for HHC include: (1) Age 18–60 years; (2) Housemate of an eligible TB case for at least the past month; (3) HIV seronegative or willing to be tested; (4) Willing to be tested for pregnancy. Exclusion criteria include: (1) Pregnant at enrollment; (2) Having known diabetes mellitus or evidence by hemoglobin A1C (HbA1c) > 6.5%; (3) GeneXpert positive among those able to produce sputum; (4) History of TB disease; (5) Karnofsky score ≤ 10 (moribund); (6) If BMI < 16 kg/m^2^, abnormal potassium, magnesium, or phosphorus; (7) Kwashiorkor; pitting edema; neuropathy [23].

All HHCs in the home are approached for enrollment. All eligible household contacts in one house are enrolled for prospective follow up if the HHCs fall in overlapping study arms. If there are more than one eligible HHCs, but no overlapping study arm designations, any malnourished HHC screened is enrolled to limit selection bias. We expect to enroll 760 HHCs to identify 120 study participants for longitudinal follow-up. Sample size was determined by participant data from the Regional Prospective Observational Research for Tuberculosis (RePORT India) cohort study [24].

### Study procedures

#### Index case and household contact enrollment

Participants are enrolled and consented at their primary healthcare center (PHC), hospital, or other place of their choosing. Laboratory evaluation of sputum for GeneXpert or AFB smear/mycobacterial culture, chest x-ray (CXR) and urine pregnancy test is conducted to determine eligibility status for ICs. Medical history, medication history, and BMI will also be collected. Index cases are not followed after that initial visit, unless the IC and enrolled HHC is malnourished then the IC will receive up to five household visits. HHCs are contacted and evaluated for study eligibility and participation 8 weeks after IC enrollment (Fig. 1). Evaluation will take place at their PHC, home, or other place of their choosing. Study staff obtain written informed consent for all ICs and HHCs. Additional consent is obtained to use stored samples for future research.

**Fig. 1 Fig1:**
[figure not shown]
Tuberculosis: Learning the Impact of Nutrition (TB LION) study schematic. *For parasite participants only, **For intervention participants only. *U* Undernourished, *WN* Well-nourished, *P* Parasite-infected

### HHC participant assessments

#### Demographics and medical history

Participants have demographic information collected at baseline and during follow up visits (months 3, 6, 12, 18 and 24). Information regarding socioeconomic status [25, 26] (Multidimensional Poverty Index and the Demographics and Health Surveys Program), alcohol consumption [27] (Alcohol Use Disorders Identification Test-Concise [AUDIT-C]), smoking history [28] (WHO Global Adult Tobacco Survey), household food insecurity [29] (USAID Household Food Insecurity Assessment Survey), quality of life [30] (36-Item Short Form Survey Instrument), and stigma [31] (Courtesy Stigma Survey) are collected as these factors may be associated with Mtb infection (Fig. 2). Participants are screened for TB symptoms at baseline and during follow up visits (bi-weekly, months 3, 6, 12, 18 and 24).

**Fig. 2 Fig2:**
[figure not shown]
Schematic of factors associated with *Mycobacterium tuberculosis* (Mtb) infection and risk of progression from Mtb infection to active TB disease with numbered references [55–80]

### Nutritional assessments

#### Anthropometry

Participants undergo anthropometric assessment (height, weight, mid-upper arm circumference, hip circumference, waist circumference, triceps and subscapular skinfold thickness, and grip strength) at baseline and during follow up visits (months 3, 6, 12, 18 and 24) [32, 33]. All measurements are taken in triplicate. Field teams have comprehensive anthropometric training; a trained dietitian from the US has conducted a week-long training, introduced each measurement tool and demonstrated taking each measurement to the site staff. Each staff member was required to pass a practical examination prior to study start and at regular intervals thereafter. Videos were made of the training sessions and are viewed at 6-month intervals by the study team.

#### Assessment of dietary intake

At enrollment/screening and follow-up visits (months 3, 6, 12, and 24), nutritionists conduct detailed 24-hfood recalls to assess dietary intake [34]. A 5-step multiple pass method, based on the USDA method, is used [35]. In step one, participants recall an uninterrupted list of all food and drink items consumed in the last 24 h probing for any forgotten items. Each item is entered into the data collection instrument, and the nutritionist reviews each list item again and collect data on portion size or quantity. The next three steps use a structured approach to collect details on preparation methods and portion sizes. Nutritionists were trained to use portion-size guide props including locally used dishes, cups, and serving utensils to serve as a visual aid for participants. Each standardized item is labeled with the appropriate milliliter or gram size, and participants are encouraged to report whether they consumed the whole or partial amounts of portions. The final step probes for forgotten foods and includes several additional memory cues.

Nutritionists collect 24-h recalls on paper forms before entering the data into a tailor-made, local food composition database housed in DietSoft (New Delhi, India). DietSoft software contains 1205 commonly consumed Indian food items including all of the foods in the India Food Composition Tables (IFCT) [36] and the National Institute of Nutrition (NIN) Nutritive Value of Indian Foods list [37], as well as several popular brand-name items. The study team also conducts extensive recipe collection in order to supplement DietSoft with common recipes relevant to the diets of people in Tamil Nadu, specifically. Recipes are collected from study participants, relevant household members, or from community members responsible for cooking (restaurant/shopkeepers and study nutritionists). When possible, recipes are collected using a direct observation method that includes measuring the weight and volume of all raw ingredients, recording details on preparation methods (e.g., frying, boiling, etc.), and measuring the weight and volume of the cooked dish. When direct observation is not possible, nutritionists collect recipes from respondents using a multiple-step method similar to the USDA 24-h recall data collection methodology [35]. For recipes with wide varieties in preparation methods, they are collected from multiple respondents to capture variability. Study nutritionists supplement the DietSoft food item list with nutrition information from commonly consumed brand-name items that were not pre-entered in DietSoft.

### Parasitology

Participants are provided with stool containers for at home stool collection during screening and follow up visits (months 1, 3, 6, and 12). Stool samples are collected in three containers containing (1) 10% formalin (for diagnostic microscopy); (2) Zn-PVA (for polymerase chain reaction [PCR] testing); and (3) RNAlater (for microbiome testing on a subset of participants). If there is a shortage of Zn-PVA, stool samples are split into two with half the sample being stored in 5–10% formalin and the other half unpreserved. QuantiFERON-TB Gold Plus (QFT-Plus) negative screened participants only have stool collected for microscopy. PCR is conducted to confirm infections with *Ancylostoma duodenale, Necator americanus, Ascaris lumbricoides, Strongyloides stercoralis*, and *Trichuris trichiura*. We define parasite infection as having one or more helminth infections. Those with helminth infections are referred to their PHC for treatment. Month 1 microscopy and PCR is conducted on QFT-Plus positive parasite study arm participants to confirm that parasite infections have resolved. The parasitology technician conducts stool concentration, sedimentation, and trichrome staining for parasite identification. All parasite positive samples and diagnostic queries undergo confirmation by the head of the parasitology department. The parasitology technician completes a quarterly external quality assurance (EQA) program (Wisconsin State Laboratory of Hygiene) [38]. All remaining samples are stored in – 80 C freezer.

### Longitudinal follow-up

HHCs that are QFT-Plus positive are placed in one of four study arms for longitudinal follow-up over 2 years (30 in each): (1) Undernourished (BMI < 18.5 kg/m^2^) with parasitic infection (UP); (2) Undernourished without parasitic infection (U); (3) Well-nourished with parasitic infection (WP) and (4) Well-nourished without parasitic infection (W). The field team will attempt to enroll participants evenly across all study arms until target numbers in each arm are met. If enrollment challenges are presented, we will extend the enrollment period by 1 year. Study staff make all attempts to retain each participant in the study via training in rapport building and behavior change as well as having frequent contact through study visits. However, participants are free to discontinue participation at any point.

Participants are evaluated at 7 additional time points after enrollment (2 weeks and months 1, 3, 6, 12, 18 and 24) to monitor change in health status and evaluate change in immune response. All HHCs are screened for TB symptoms at every visit. If a HHC develops TB symptoms at any visit, sputum, blood, and stool samples are collected and the HHC is referred to NTEP for evaluation. Participants who cannot be reached after three contact attempts (on varying days and times) are moved off study and considered lost to follow up. Case report forms assess potential adverse reactions to the intervention, and study staff are trained to report any adverse event to the Principle Investigators (PIs) who determine the correct reporting path to their respective review boards.

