The field team visits households every other week to replenish the food, assess food consumption and changes in participant health. During the initial food delivery visit, nutritionists provide study food containers and then weigh each container, taring the scale to accurately account for the weight of container. They then add the calculated amount of each food item and mark each container with a black marker to indicate the fill line. The weight of each respective food container is recorded. Nutritionists return to the household every 2 weeks to evaluate the remaining food and vitamin supplement. The remaining food (for each item) is poured into a tared tray, weighed and recorded. Using the initial calculated food quantity and remaining quantity, nutritionists calculate the amount of food consumed by the household and the amount required to replenish the stock which is added to the container before the remaining food to minimize food expiry.

Severely undernourished participants (BMI 14–16) receive partial supplementation for the first 2 weeks of intervention; 30% for the first week and 50% the second week. By the third week, participants will receive 100% of the supplementation. Study staff assess electrolytes (potassium, magnesium, and phosphorus) and conduct an assessment for food consumption and changes in participant health before replenishing the week’s food supply. If electrolyte results are normal, food supply is increased; however, if food is not being consumed based on observation, a second week of the partial ration is provided and electrolytes re-checked. If electrolyte results are abnormal, food supplementation is stopped, and the participant is referred to the hospital. HHC bi-weekly visits detailed above will begin once 100% of the ration is received.

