### Statistical analyses

#### Mtb killing, cytokine analyses, and cellular immune responses

For the Mtb killing (intracellular bacterial growth) assays, we will log-transform relative luminescence units and compare groups using ANOVA including nutrition status, parasite status, gender and any other significant covariate using a forward selection approach. For all analyses, if needed (e.g. skewed or bimodal data), we will apply a non-parametric Kruskal–Wallis test. For colony forming unit measurements, we will use a Poisson regression model that includes covariates using a forward selection approach. For cytokine analyses, markers will be compared using ANOVA or Kruskal–Wallis test. If needed, to correct for multiple comparisons, we will apply a Bonferroni adjustment. To understand the effect of parasite treatment and nutritional supplementation over time, we will use time-course repeated measurements on the same individual and a mixed linear model.

The predictive value will be evaluated by receiver operating characteristics (ROC) curve analysis and logistic regression modeling using covariate metadata. Because our preliminary data demonstrate a strong signal from these markers, we will split our cohort into a training set (n = 20 in each group) and a test set (n = 10 in each group) for cross-validation purposes. The markers will be evaluated for their predictive abilities individually, as well as in combination. The combination logistic regression biomarker will be selected using a forward-step approach, adding markers one at a time and evaluating the predictive value (cross-validation within the training set).

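### Three failed contact attempts take a participant off study, with no stated time window and no route back, so a temporary absence can end follow-up

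*Protocol article*

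**What the plan says.** All references are to the protocol article.

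- *Longitudinal follow-up*, the rule: "Participants who cannot be reached after three contact attempts (on varying days and times) are moved off study and considered lost to follow up". Voluntary discontinuation has its own sentence, so this is a second way out, applied by the study team.
- Same section, intent: "Study staff make all attempts to retain each participant in the study".
- Same section, arms: contacts positive on QFT-Plus are "placed in one of four study arms for longitudinal follow-up over 2 years (30 in each").
- Same section, schedule: "Participants are evaluated at 7 additional time points after enrollment (2 weeks and months 1, 3, 6, 12, 18 and 24").
- *Study population*: "We expect to enroll 760 HHCs to identify 120 study participants for longitudinal follow-up".
- *Statistical analyses*, for the effect of parasite treatment and supplementation over time: "we will use time-course repeated measurements on the same individual and a mixed linear model". *RNA sequencing* plans a mixed model for repeated measures as well.
- *Specimen handling and storage*: plasma, serum and whole blood are taken serially over 1 year.
- *Sample size calculations*: 30 per group is justified by biomarker performance and estimation error. No allowance for dropout is stated.

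**The concern.** A definition of loss to follow-up normally describes people who could not be recovered by the end of the study. Here the rule also acts during follow-up: once three attempts fail, the participant is taken off the study. The sentence does not tie the attempts to a visit window and does not say that someone who reappears may continue. Staff following it as written would have no reason to try again at the next visit, which from month 6 onward is 6 months later. A person away for a short time could then lose every later visit without having withdrawn.

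This sits badly with two other parts of the plan. The same paragraph promises every effort to retain participants. The longitudinal analyses use mixed models, which can include a participant who misses one visit and attends the next, so the rule can forgo data that the analysis could use. With 30 per arm and no stated allowance for dropout, there is little slack for avoidable loss.

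**Working it through.** **The plan's own figure.** 4 arms × 30 = 120, which agrees with *Study population*. The article states no alpha, power, target effect or dropout rate behind the 30, so there is no power statement to reproduce.

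**Inputs**
- Arm size n = 30 (*Longitudinal follow-up*).
- Scheduled follow-up visits: 2 weeks and months 1, 3, 6, 12, 18 and 24. Month 12 is the fifth.
- Scheduled blood sampling runs over 1 year (*Specimen handling and storage*), so month 12 is the relevant end point for the immune and RNA repeated measures.
- q, the chance of being unreachable at a visit, is **assumed**, because the article gives no rate. Absences are also **assumed** independent across visits.

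**Formulas for participants available at month 12**
- Rule read as removal at the first unreachable visit: 30 × (1 − q)^5.
- Missed visit only, participant stays eligible: 30 × (1 − q).

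| q (assumed) | Rule as written | Missed visit only | Difference |
|---|---|---|---|
| 1% | 30 × 0.99^5 = 28.5 | 30 × 0.99 = 29.7 | 1.2 |
| 2% | 30 × 0.98^5 = 27.1 | 30 × 0.98 = 29.4 | 2.3 |
| 3% | 30 × 0.97^5 = 25.8 | 30 × 0.97 = 29.1 | 3.3 |
| 5% | 30 × 0.95^5 = 23.2 | 30 × 0.95 = 28.5 | 5.3 |

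**Sensitivity to independence.** If the same people were unreachable at every visit, both rules would leave 30 × (1 − q) and the difference would be zero. Clustering therefore moves the result from the last column towards zero. The same holds if some unreachable people have left for good, since no rule brings them back.

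**Beyond month 12.** Symptom screening continues to month 24, the seventh visit. There 30 × (1 − q)^7 gives 26.0, 24.2 and 21.0 at q = 2%, 3% and 5%. These counts concern clinical follow-up only. They are not sample sizes for an immune comparison, because the article describes no scheduled blood sampling that late.

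**The case against.** Three attempts on varying days and times is an ordinary working definition of loss to follow-up. The article neither says that one visit is enough nor forbids return, and a condensed article may leave contact windows and re-entry to the full protocol. This stands as a limit on the claim: that a single missed visit removes a participant permanently is an inference from a plain reading, not something the text states. It does not remove the point. The article does state the consequence of failed contact, namely removal from the study, and that consequence is what should change.

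Several stronger conclusions are tempting and are not supported.

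- *A loss of power or a larger detectable difference at month 24.* Scheduled blood sampling covers 1 year. A mixed model also keeps all visits before dropout, so an arm with 21 completers is not analysed as a two-sample comparison with 21. Baseline comparisons between arms lose nothing.
- *Loss that differs by arm.* In the intervention, "The field team visits households every other week to replenish the food", and other participants lack these contacts. But the food visits end after 6 months, and the long gaps come later, when the stated schedule is common to all arms. More contact could help retention or give more occasions to apply the rule. The article shows neither, and the proposed wording would not remove the difference in contact.
- *Loss of a defined 24-month TB endpoint.* Progression is a hypothesis in *Study expectations*, but the stated aims and outcomes are immune and transcriptomic, and no analysis of TB status at month 24 is specified.

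**Conclusion.** The point holds in a limited form. As written, the rule turns failed contact into removal from the study, with no window and no provision to resume. It can therefore give up later visits that the planned models could use, in arms of 30 with no stated dropout allowance.

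The size is illustrative. At month 12 the avoidable loss is about 1 to 2 participants per arm at 1–2% unreachable per visit, and about 5 at 5%. This rests on the assumed rates, on independent absences, and on unreachable people being contactable again later. Clustered absences or true departures make it smaller. The case for change does not need the higher figures: the change is cheap, and it brings the rule into line with the stated retention aim and the planned analysis. It should be made, but nothing here shows that the trial's conclusions would fail without it.

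**What to change.** Replace the sentence in *Longitudinal follow-up* with:

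> After three failed attempts within the visit window the visit is recorded as missed. Unless consent is withdrawn, the participant stays in the study and is contacted again at each later scheduled visit. Loss to follow-up is assigned only at the end of follow-up.

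The full protocol should state the length of the visit window. If it already does so, and already allows participants to resume, the article's sentence need only be brought into line.

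Cost: a few more contact attempts at later visits, with no change to assessments or analysis.

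Optional: look up the TB status of unreachable participants in programme records. The article describes working with the programme to find index cases ("Study staff identify new TB index cases (ICs) through the National Tuberculosis Elimination Programme (NTEP")) and to refer contacts with symptoms. It does not establish consent or access for linking contacts to those records, so this would be a new step subject to both.
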